### Interim analyzes and stopping guidelines

Serious and unexpected adverse events will be reported according to recommendations given by the Consort Group. For the RTSA intervention group the primary focus will be postoperative infections, prosthesis dislocation, loosening of the glenosphere or the humeral stem and signs of scapular notching. Healing of the tubercles and signs of deltoid muscle dysfunction constitute secondary items. In the Philos group primary items will be postoperative infection and implant failure as pull-out and cut-out of the screws. The definition of infection is: a) Less serious infection: Superficial wound infection with sign of skin inflammation and/or a positive bacterial culture, without call for re-surgery. b) Serious infection: Any postoperative wound infection or sign of deep infection that call for re-surgery.

At 18 months an independent researcher from the main hospital OUS Orthopaedic Research Department will evaluate the complication rates and for the attending centers and correlate them to expected rates in the available literature. An unexpected high rate of complications in either group will be reported to the project group, deciding whether the randomization need to be closed.

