The early reports of treatment with ORIF using angular stable plates were promising [44]. Later, however, it has become evident that although the angular stable implants contributed to the surgical management of severely displaced fractures, several problems and pitfalls stayed unsolved. The method of fixation utilizing an angular stable plate caused a disappointing number of complications, as cut-out of screws into the joint space, avascular humeral head necrosis, non-union, and varus malalignment [45–49]. Some of these complications are caused by poor surgical technique, and may be avoidable [50]. Supplemental tension band fixation and restoration of the medial calcar may improve outcome and decrease the incidence of hardware-related complications [20, 22, 51].

Head replacement or shoulder hemi-artroplasty (HA) has been used as a treatment option for three decades, and has been claimed a better option than open reduction and fracture fixation in certain severely displaced and dislocated intracapsular fractures, even though the evidence is still not conclusive. Some related important problems are well known: Poor rotator cuff status and non-union of the tubercles. If these main problems are avoided, patients may have a good outcome with these implants [41]. In the elderly patient suffering a proximal humeral fracture, however, the status of the rotator cuff frequently is poor [42, 43, 52, 53]. A recent randomized study concluded that head replacement did not prove better than conservative treatment [35], and several other authors also report unsatisfactory results with hemi-arthroplasty; Loss of ROM, non-union of tubercles in as many as 50% of the patients in some series and poor quality of the rotator cuff result in inferior functional outcome [28, 41, 54, 55].

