A more recent treatment option for displaced proximal humeral fractures is the reverse total shoulder artroplasty (RTSA). It was introduced nearly 20 years ago in treatment of acute proximal humeral fractures [56]. During the last decennium the use of RTSAs has increased, both as a salvage procedure after failed hemi-artroplasty but also in the primary fracture care. RTSA has gained popularity and has showed promising results in the treatment for proximal humeral fractures in the elderly patients [57–59]. A small level 2 study was recently reported [39], concluding that RTSA showed similar outcome to HA, but functional outcome was more predictable. The advantage of the concept is less dependence on a normal rotator cuff, as the elderly population frequently suffer asymptomatic degenerative cuff tears leading to a poor prognosis [60]. However, problems with RTSA have been reported, mainly instability, poor rotation and fatigue of the deltoid muscle with time [56]. Also, radiological notching of the glenoid is frequent, but has not proven clinically important in the older Delta III prosthetic designs [61]. Due to these problems and complications the RTSA has until recently only been advocated in older patients [37]. Recently improved prosthetic designs possibly have reduced the problem of notching, due to overhang of the scapular component [62].

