The RTSA principle has been developed during the last three decades [56, 82] reducing the problems of nonunion and/or resorption of the tubercles, a main problem flawing hemi-artroplasties [40]. Reducing the importance of the rotator cuff may, however, create increased load on the deltoid muscle and change the biomechanics of the glenohumeral joint. The potential problems with overload of the deltoid muscle and loosening of the glenosphere have been pointed out [38], and these problems certainly need further elucidation. Although several complications have been reported, the prostheses used in many of these studies are older RTSA designs, and the surgical indications mostly refer to patients going through revision surgery or rotator cuff defiencies [58]. In a short five years perspective RTSA may turn out to be a better and more predictable option than other prostetic replacements and ORIF, also in a health economic perspective [82]. However, in addition to this protocol including five years follow-up, we aim to follow these patients for ten years, to obtain information on long term RTSA survival after treatment of proximal humeral fractures.

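### The one planned safety look compares complications only with literature rates; add a by-arm comparison on a common list, because the protocol itself doubts how well much of the RTSA literature fits

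*Protocol article*

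**What the plan says.** The section on interim analyses and stopping guidelines plans one look, at 18 months, by an independent member of the main hospital's research department, who "will evaluate the complication rates and for the attending centers and correlate them to expected rates in the available literature". Those literature rates are the only yardstick that the section states. The consequence is "An unexpected high rate of complications in either group will be reported to the project group, deciding whether the randomization need to be closed". The section gives no benchmark figures and mentions no comparison between the randomised arms.

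The items differ by arm. For RTSA the primary focus is infection, prosthesis dislocation, loosening of the glenosphere or stem, and scapular notching; tubercle healing and deltoid dysfunction are secondary. For the plate, "In the Philos group primary items will be postoperative infection and implant failure as pull-out and cut-out of the screws". Infection is defined once, for both arms, and its serious form is one that leads to further surgery.

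Three other statements bear on this:

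- Discussion, on RTSA complication reports: "the prostheses used in many of these studies are older RTSA designs, and the surgical indications mostly refer to patients going through revision surgery". Deficiency of the cuff is named there as the other main indication.
- Background, on RTSA: "radiological notching of the glenoid is frequent, but has not proven clinically important". The sentence goes on to limit this to the older Delta III designs.
- Background, on angular stable plates: besides screw cut-out, the complications named include "avascular humeral head necrosis, non-union, and varus malalignment".

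**The concern.** The trial has a randomised concurrent control: same hospitals, same fracture types, same follow-up and same assessors. That is the natural reference for excess harm, yet the look that can close randomisation is described without it. Each arm is set against outside rates instead.

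For RTSA the protocol itself gives reason to doubt those rates. If they come largely from older implants or from revision patients, and if such patients have more complications, a worrying RTSA rate in acute fractures could look unremarkable.

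The item lists make it hard to repair this afterwards. Only infection appears in both. Unplanned reoperation for any other cause is in neither. A reader of the 18-month report could not set the arms side by side on the listed items.

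**Working it through.** The safety look has no figure of its own to reproduce, and the documents give no complication rates. All rates below are assumptions, used to show how the look behaves.

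**Size of the look.** The inclusion timeline expects 40 patients a year. Counting 18 months from the start of inclusion, 40 × 1.5 = 60 patients, or 30 per arm with equal allocation. Fewer will have useful follow-up.

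**Dependence on the benchmark.** Take n = 30 in one arm. Flag when the event count reaches the smallest r with P(X ≥ r | n = 30, benchmark rate) ≤ 0.05. With a true rate of 30%, the chance of a flag is P(X ≥ r | n = 30, 0.30):

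| Benchmark | Flag at r or more | Chance of a flag |
|---|---|---|
| 10% | 7 | 84% |
| 15% | 9 | 57% |
| 20% | 11 | 27% |
| 25% | 13 | 8% |
| 30% | 14 | 4% |

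The same true rate is flagged most of the time or almost never, depending on which papers supply the benchmark.

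**What a between-arm comparison offers.** With 30 v 30, sum the product of the two binomial probabilities over all pairs of counts that reach significance.

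| Assumed rates | Test | One-sided 0.05 | One-sided 0.10 |
|---|---|---|---|
| 30% v 15% | Pooled z | 42% | 56% |
| 30% v 15% | Fisher exact | 28% | 42% |
| 40% v 15% | Pooled z | 72% | 83% |

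**Like with like.** Against a sound 15% benchmark, the one-arm exact test detects a true 30% with probability 57% at 0.05 and 72% at 0.10. The pooled-z comparison at the same levels gives 42% and 56%. With a well-chosen benchmark, then, the literature check is the more sensitive of the two. With a 25% benchmark it falls to 8% at 0.05, and the between-arm result is unchanged because it uses no outside rate.

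**False flags.** With both arms at 15%, the pooled z at one-sided 0.10 flags 10.7% of the time in each direction. Looking both ways gives 2 × 10.7% ≈ 21%.

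**The lists side by side.**

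| Item | RTSA list | Plate list |
|---|---|---|
| Infection (one definition) | yes | yes |
| Dislocation, loosening | yes | not applicable |
| Screw pull-out, cut-out | not applicable | yes |
| Notching | yes | not applicable |
| Head necrosis, non-union, varus malalignment | not applicable | not listed |
| Reoperation for causes other than infection | not listed | not listed |

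Head necrosis, non-union and head inclination are nevertheless scored for the plate arm under the radiographic items for ORIF.

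**The case against.** The strongest reply is that the benchmark problem is inferred. The safety section refers to the available literature in general and does not tie itself to the studies criticised in the Discussion. The Background cites RTSA reports in primary fracture care, so an acute-fracture benchmark is open to the researcher. The Discussion's remark that revision and sequelae cases do less well concerns survivorship after 8–10 years, and its statement that primary replacement does better than revision is about results in general. Neither is about early complication rates. All of this stands: the direction of any bias is not established. It does not remove the point, because nothing in the section directs the researcher to the better-matched sources or to the concurrent arm.

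Several stronger readings are tempting and are not supported:

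- **That both benchmarks are compromised.** The caution covers RTSA only, and only many of those studies. Nothing in the documents questions the plate literature.
- **That notching inflates the RTSA rate.** No pooled rate is defined, and notching set against published notching rates inflates nothing. The remark that notching is not clinically important is limited to the older Delta III, whereas this trial uses the Delta Xtend.
- **That the plate arm's known complications go unrecorded.** The lists are labelled as primary items, the look is not confined to them, and the radiographic scoring covers head necrosis and non-union.
- **That this is the only safety reporting.** Serious and unexpected events are also reported separately and prompt registry updates. It is the only planned look.
- **That a between-arm test should replace the literature check.** It would lose power where the benchmark is sound, and it cannot see a rate that is too high in both arms, which the existing trigger on either group can.

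Benchmark values and thresholds may sit in the full protocol, which is not shown, and their absence from the article is not the complaint. The complaint is the stated choice of comparator.

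**Conclusion.** The point holds in a limited form. The only planned look that can close randomisation uses literature rates as its sole stated comparator, and the protocol says that much of the RTSA complication literature comes from other designs and indications. The listed items share only infection, so they give no common basis for comparing the arms.

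Under assumed rates and 30 patients per arm, moving the benchmark from 15% to 25% cuts the chance of flagging a true 30% from 57% to 8%. That shows sensitivity to the benchmark. It does not show that the benchmark will be too high. The conclusion rests on accrual as planned, on 18 months being counted from the start of inclusion, and on rates that the documents do not supply. It is worth acting on because the remedy is cheap, but it supplements the present plan and does not overturn it.

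**What to change.** Keep the literature check, preferably with acute-fracture sources, and name those sources. Add to the 18-month report a table by randomised arm, with confidence intervals for each rate and for the difference, on one list applied to both arms: serious infection (as already defined), any unplanned reoperation, and implant failure or dislocation. The independent researcher reports it to the project group. Notching, head necrosis and the other implant-specific radiographic items are reported separately.

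State the limits with the table. At 30 per arm its power is modest, and a one-sided 0.10 flag used in each direction would be false about one time in five when the arms are equal. It therefore supports the project group's judgement and is not a stopping rule.

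The cost is a few sentences and one table. Infection, implant failure and dislocation are already recorded; reoperations need to be tabulated for all causes. No extra visits or staff are needed.

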### Trial registration

Trial has been reported on the http://www.ClinicalTrial.gov before inclusion started, and update will take place during the inclusion and follow-up if any serious unexpected events occur, and after completed inclusion of patients. ClinicalTrials.gov Identifier: NCT01737060.

### Consort statement

The study will be reported according to the Consort statement [4]. (http://www.consort-statement.org) A flow chart will be presented in line with the Consort recommendation Figure 3.

**Figure 3 Fig3:**
[figure not shown]
**Flow chart DELPHI- trial.** Timeline.

## Discussion

This protocol has been designed according to recommendations given by the Consort group [4]. The design of a randomized controlled study with a high level of evidence including more than 100 patients, with semi-blinded independent physical therapists collecting patient data gain important knowledge about proximal humeral fractures. A standardized surgical approach for both groups without compromising the deltoid muscle, reduces group differences, and a standarized educational program for all physiotherapists prior to examination of patients at follow-up contribute to a better methodological design and strengthen this study.

This study protocol has been adjusted according to our experience from former studies, both regarding outcomes, method of randomization and exclusion criterias [16, 17]. Also, to gain knowledge of the external validity of this study, all patients aged 65 to 85 years admitted to two of the recruiting hospitals will be grouped according to the exclusion criteria and AO classification, hopefully increasing our knowledge of the generalizability of our results. This generalizability and the question if the results of this trial will cause impact in the future treatment of displaced B2 and C2 proximal humeral fractures is a basic issue when a new trial is designed. Although it is more than 40 years since Charles Neer wrote his two important papers on classification and treatment of proximal humeral fractures, these papers are still frequently referred and the treatment is still under debate [1, 2]. The sparse number of studies at the highest level of evidence may be one of the reasons.

The trial may have potential weaknesses: Blinding of a trained physiotherapist examining a patient with a prosthetic replacement is difficult due to the mechanics of the implant. Another potential problem is that the primary outcome (Constant score) has a low reproducibility between different observers in a multicenter trial [67, 68]. However, the pre-trial training for all participating physiotherapists will reduce this bias.

Concerning the surgical treatment, not all parts of the treatment can be standardized, and may represent confounders. For the ORIF procedure the different fracture patterns, as well as the use of a medial calcar butress plate, may confound outcome. However, the surgeons perioperative individual judgement of the technically best treatment solution will have priority. All adjuvant treatment in addition to the Philos plate and thread cerclages around the tubercles will be reported.

Current recommendations in the litterature advise the use of reversed total shoulder arthroplasty in patients aged over 70 years [37]. Even so, the lower age limit in this trial has been set to 65 years. An acute proximal humeral fracture clearly represents a different problem compared with a planned revision of a failed arthroplasty or sequela after a malunited fracture. Kaplan-Meier survivorship analysis has showed acceptable outcomes for cuff tear arthropaties, while revision arthroplasties and fracture sequelae show less favourable results after 8–10 years [78, 79]. Primary joint replacement after fracture of the proximal humerus has gained better results than secondary revision arthroplasty, and hemi-arthroplasty give less predictable results than RTSA [39]. Thus, the youngest patients group in this trial may obtain a more predictable shoulder function for the next 8–10 years after a RTSA compared to using other prosthetic modalities. Therefore a potential decline in QoL will be delayed and possibly minimized, as older persons usually will have a natural decline in shoulder function and lower demand with higher age.

Some ongoing and recently completed trials deals with the issue of best treatment of proximal humeral fractures. Two recent randomized controlled trials of four-part humeral fractures treated either non-operatively or with hemiarthroplasty, could not show differences between the treatment groups at one year [80, 81]. Neither could our former trial comparing ORIF and non-operative treatment for three- and four part fractures prove any difference in favor of one of the treatments [16, 17].

However, no study has yet, to our knowledge, compared RTSA and ORIF. The only known trial comparing RTSA with another surgical option, is a small level 3 study, concluding that RTSA outperformed hemi-arthroplasty with regard to all outcomes measures assessed [57].

The RTSA principle has been developed during the last three decades [56, 82] reducing the problems of nonunion and/or resorption of the tubercles, a main problem flawing hemi-artroplasties [40]. Reducing the importance of the rotator cuff may, however, create increased load on the deltoid muscle and change the biomechanics of the glenohumeral joint. The potential problems with overload of the deltoid muscle and loosening of the glenosphere have been pointed out [38], and these problems certainly need further elucidation. Although several complications have been reported, the prostheses used in many of these studies are older RTSA designs, and the surgical indications mostly refer to patients going through revision surgery or rotator cuff defiencies [58]. In a short five years perspective RTSA may turn out to be a better and more predictable option than other prostetic replacements and ORIF, also in a health economic perspective [82]. However, in addition to this protocol including five years follow-up, we aim to follow these patients for ten years, to obtain information on long term RTSA survival after treatment of proximal humeral fractures.

## Abbreviations

RTSA: Reversed Total Shoulder Arthoplasty
Philos: Proximal Humeral Internal Locking System
DELPHI: The Delta-Philos trial
HA: Hemi Arthroplasty
AO-OTA: Arbeitsgruppe für Osteosynthesefragen - Orthopaedic Trauma Association
CSD: Constant Score Difference
OSS: Oxford Shoulder Score
15D: 15 Dimensional Helath Related Quality Of Life form (Harri Sintonen)
HQoL: Helath Related Quality Of Life
QALY: Quality Asjusted Life Years
ROM: Range Of Movement
MCID: Minimal Clinically Important Difference.
